# Direct antivirals working against the novel coronavirus: azithromycin (DAWn-AZITHRO), a randomized, multicenter, open-label, adaptive, proof-of-concept clinical trial of new antivirals working against SARS-CoV-2—azithromycin trial

**DOI:** 10.1186/s13063-021-05033-x

**Published:** 2021-02-09

**Keywords:** SARS-CoV-2, COVID-19, Azithromycin, Macrolide, Antiviral, Randomized controlled trial

## Abstract

**Background:**

The rapid emergence and the high disease burden of the novel coronavirus SARS-CoV-2 have created a medical need for readily available drugs that can decrease viral replication or blunt the hyperinflammatory state leading to severe COVID-19 disease. Azithromycin is a macrolide antibiotic, known for its immunomodulatory properties. It has shown antiviral effect specifically against SARS-CoV-2 in vitro and acts on cytokine signaling pathways that have been implicated in COVID-19.

**Methods:**

DAWn-AZITHRO is a randomized, open-label, phase 2 proof-of-concept, multicenter clinical trial, evaluating the safety and efficacy of azithromycin for treating hospitalized patients with COVID-19. It is part of a series of trials testing promising interventions for COVID-19, running in parallel and grouped under the name DAWn-studies.

Patients hospitalized on dedicated COVID wards are eligible for study inclusion when they are symptomatic (i.e., clinical or radiological signs) and have been diagnosed with COVID-19 within the last 72 h through PCR (nasopharyngeal swab or bronchoalveolar lavage) or chest CT scan showing typical features of COVID-19 and without alternate diagnosis. Patients are block-randomized (9 patients) with a 2:1 allocation to receive azithromycin plus standard of care versus standard of care alone. Standard of care is mostly supportive, but may comprise hydroxychloroquine, up to the treating physician’s discretion and depending on local policy and national health regulations. The treatment group receives azithromycin qd 500 mg during the first 5 consecutive days after inclusion. The trial will include 284 patients and recruits from 15 centers across Belgium. The primary outcome is time from admission (day 0) to life discharge or to sustained clinical improvement, defined as an improvement of two points on the WHO 7-category ordinal scale sustained for at least 3 days.

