### Primary outcome

The primary outcome is the time from admission/randomization (day 0) to sustained clinical improvement or live discharge, whichever comes first, whereby a sustained clinical improvement is defined as an improvement of > 2 points vs the highest value of day 0 and 1 and sustained for at least 3 days.

The clinical status is recorded on a 7-point ordinal scale:
Not hospitalized, no limitations on activities;Not hospitalized, limitation on activities;Hospitalized, not requiring supplemental oxygen;Hospitalized, requiring supplemental oxygen;Hospitalized, on non-invasive ventilation or high flow oxygen devices;Hospitalized, on invasive mechanical ventilation or ECMO; andDeath.

This ordinal scale was chosen in compliance with the WHO master template and to facilitate data pooling with other studies. A 2-point improvement has been used in other COVID trials [20] as a robust and clinically relevant outcome. Concretely, in clinical practice, this 2-point improvement implies that a patient who is admitted to the ICU has at least been downgraded to a non-intensive care ward, and a patient who was admitted to the hospital on a normal ward has been discharged.

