#### Sample size {14}

As in other COVID trials [20], the time to reach a 2-point improvement on the WHO ordinal scale was chosen as the primary outcome. While azithromycin is generally safe, some concerns have been raised with the large-scale use in COVID-19, e.g., a possible increase of cardiac adverse events when combined with other QT-prolonging drugs such as hydroxychloroquine or increased bacterial resistance. While the exact proportions of such harms are not yet clear, we deemed that a sufficiently low number needed to treat was necessary to outweigh these potential risks and for the trial results be truly clinically meaningful. An absolute risk difference of 15 to 20% (correlating to a single-digit number needed to treat [NNT] between 7 and 5) therefore seemed appropriate. In concrete clinical terms, this means the following: Based on the control group of the Lopinavir-Ritonavir trial of Cao et al. [20] that used the same ordinal scale and had a similar population, we can assume a 2-point improvement on the ordinal scale will be observed in 40% of patients with standard of care at day 15. An absolute risk difference of 15% or 20% means that respectively 55% or 60% instead of 40% will have reached the primary endpoint in the azithromycin-treated group at day 15.

Based on the log-rank test, with a 2-sided significance level of 5 and 80% statistical power and using a (2:1) randomization ratio in favor of azithromycin, a total sample size of 354 patients would suffice to detect an absolute risk difference of 15%. To detect an absolute risk difference of 20%, a total sample of 196 patients would suffice. We propose a pragmatic sample size of 282 patients taking into account early dropouts. Two hundred fifty-eight patients will be sufficient to detect an absolute improvement of 17.5% with a statistical power of 80% at a 2-sided significance level of 5%.

Although it should be balanced against potential harms, we acknowledge that a larger NNT might also still be clinically relevant due to the scale of the pandemic. This emphasizes the importance of adhering to internationally promoted outcome measures like the WHO ordinal scale, to facilitate data pooling afterwards.

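### The Primary outcome section requires an improvement of more than 2 points, while the abstract, the section's own explanation and the sample-size basis all use 2 points; the definitions differ only for patients starting in category 5 or 6.

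*Protocol article*

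**What the plan says.** The improvement component of the primary outcome is described in four places.

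- **Abstract, Methods:** improvement is "defined as an improvement of two points on the WHO 7-category ordinal scale sustained for at least" three days, with live discharge as the alternative event.
- **Outcomes {12}, Primary outcome, first paragraph:** "an improvement of > 2 points vs the highest value of day 0 and 1 and sustained for at least 3 days".
- **Same section, paragraph after the scale:** "A 2-point improvement has been used in other COVID trials [20] as a robust and clinically relevant outcome". It then explains the 2-point change in practice: an ICU patient has at least moved to an ordinary ward, and a ward patient has gone home.
- **Sample size {14}:** "the time to reach a 2-point improvement on the WHO ordinal scale was chosen as the primary outcome", with 40% of standard-of-care patients assumed to show that improvement by day 15.

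The primary event is a composite: "sustained clinical improvement or live discharge, whichever comes first".

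On enrolment, the abstract says "The trial will include 284 patients and recruits from" 15 centres, while Sample size {14} says "We propose a pragmatic sample size of 282 patients".

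**The concern.** The ordinal scale takes whole numbers, so more than 2 points means 3 or more. The section that formally defines the endpoint is therefore stricter than every other statement of it in the article, including its own explanation two paragraphs later. Anyone who programs the event from the Primary outcome section will not count some patients whom the abstract, the rationale and the sample-size basis would count.

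Three things depend on it:

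- the single definition of the primary event in an open-label trial whose SAP is to be finalized only before database lock;
- the severe-disease results, since Outcomes {12} promises all outcomes separately by baseline severity and section {20b} plans an interaction test by severity;
- comparability with other trials that used a 2-point change, which the article gives as a reason for choosing this scale.

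**Working it through.** **1. Which patients are affected.** Categories 1 and 2 are out of hospital, 3 to 6 are in hospital, 7 is death. The reference is the worse of days 0 and 1. Live discharge counts as an event under either threshold.

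| Reference category | First in-hospital move counted under ≥ 2 | First in-hospital move counted under > 2 | Difference |
|---|---|---|---|
| 3 | none (3 to 1 is already discharge) | none | none |
| 4 | none (4 to 2 is already discharge) | none | none |
| 5 | 5 to 3 | none (5 to 2 is already discharge) | sustained 5 to 3 |
| 6 | 6 to 4 | 6 to 3 | sustained 6 to 4 |

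Under > 2, the improvement component adds to live discharge only for the 6-to-3 move. The section's own ICU-to-ward illustration is met by 6 to 4, which > 2 excludes. Categories 5 and 6 are within the trial population: Eligibility criteria {10} admits ventilated patients and patients on ICU wards.

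Patients who make such a move are not necessarily lost as events. Many will be counted later, at discharge or on reaching category 3, so part of the effect is delay.

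**2. Reproducing the plan's sample sizes on the 2-point basis.** Inputs from Sample size {14}: log-rank test, two-sided 5%, 80% power, 2:1 allocation, control rate p1 = 40% at day 15.

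- Hazard ratio: HR = ln(1 − p2) / ln(1 − p1)
- Events: D = (1.960 + 0.842)² / [(2/9) × (ln HR)²]
- Average event rate: (p1 + 2 × p2) / 3
- Total N = D / average event rate

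| p2 | HR | D | Average rate | N computed | N stated |
|---|---|---|---|---|---|
| 55% | 1.563 | 177.0 | 0.500 | 354.0 | 354 |
| 57.5% | 1.675 | 132.7 | 0.517 | 256.9 | 258 |
| 60% | 1.794 | 103.5 | 0.533 | 194.0 | 196 |

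The stated sizes are right for a 40% control rate, which the article ties to a 2-point improvement. It gives no control rate for a change of more than 2 points.

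**3. What > 2 could cost.** Let s be the share of patients in categories 5–6, and f the fraction of those who by day 15 have made a sustained 5-to-3 or 6-to-4 move but have neither reached a 3-point gain nor been discharged. The control rate then falls by s × f. Neither quantity is in the article, so the reductions below are assumptions. HR is held at 1.675 and p2 = 1 − (1 − p1)^HR. Power = Φ(√(N × average rate × 2/9) × ln HR − 1.960).

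| Control rate | Reduction (s × f) | Power, N = 258 | Power, N = 282 |
|---|---|---|---|
| 40% | 0 | 80.2% | 83.5% |
| 39% | 1 point | 79.3% | 82.7% |
| 38% | 2 points | 78.4% | 81.9% |
| 36% | 4 points | 76.4% | 80.0% |
| 30% | 10 points | 69.5% | 73.3% |

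A 2-point reduction corresponds, for example, to s = 20% and f = 10%. A 10-point reduction at s = 20% would need f = 50%: half of the category 5–6 patients improving by exactly two categories and no further. That row is an outer bound.

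**4. Enrolment target.** From 258 to 282 the allowance is 1 − 258/282 = 8.5%; to 284 it is 1 − 258/284 = 9.2%. Power at 40% versus 57.5% is 83.5% at 282 and 83.8% at 284, a gap of about 0.3 points.

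**The case against.** **The symbol is probably a slip.** The rest of the Primary outcome section, the abstract and Sample size {14} all point to at least 2 points, and the full protocol, which is not shown, may print it correctly. This is persuasive about intent, and it makes the correction straightforward. It does not remove the contradiction: the sentence at fault is the formal definition, and the article prints ≥ and ≤ correctly under Eligibility criteria {10}, so a text-extraction error is unlikely.

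**The data are not at risk.** Status is recorded daily in hospital, so either threshold can be derived later and a pooled analysis could use 2 points. That stands. The trial's own primary result would still rest on whichever threshold was programmed.

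**A reader might infer that the trial was sized on a different endpoint and is therefore underpowered.** The article does not support this. Its sample-size arithmetic reproduces, the threshold is irrelevant for categories 3 and 4, and no case mix is given from which a material loss could be shown. It would also be wrong to say that category 3 or 4 patients cannot reach the primary event under > 2; they reach it by live discharge.

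**A reader might link the two enrolment figures to the endpoint conflict.** They are unrelated: neither 282 nor 284 bears on which event is analysed.

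**Conclusion.** The contradiction is real and sits in the definition of the primary event, so it has to be corrected. Its reach is narrow: only sustained 5-to-3 and 6-to-4 moves are treated differently. The overall loss of power is probably modest. At a fixed hazard ratio of 1.675 it is under 2 points if the control rate falls from 40% to 38%, and about 3.5 to 4 points if it falls to 36%. These figures assume proportional hazards and an assumed fall in the control rate; the share of category 5–6 patients that would determine it is not stated. Within the severe-disease results the effect is proportionally larger, because every affected patient is there. The sample-size calculation is not in error. The 284 versus 282 difference is a separate editorial matter.

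**What to change.** In Outcomes {12}, Primary outcome, define sustained improvement as an improvement of at least 2 points (≥ 2) against the worse of days 0 and 1, sustained for at least 3 days. Use the same wording in the abstract, the SAP and the endpoint program, and settle it before database lock. The 40% planning rate and the stated sample sizes then apply unchanged.

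As a separate editorial correction, give one enrolment target throughout. The sample-size section, where the number is derived, has 282; the abstract should agree with it.

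The cost is a wording change and a check of the endpoint code. No new data and no new sample-size calculation are needed.

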**Discussion:**

The trial investigates the urgent and still unmet global need for drugs that may impact the disease course of COVID-19. It will either provide support or else justify the discouragement of the current widespread, uncontrolled use of azithromycin in patients with COVID-19. The analogous design of other parallel trials of the DAWN consortium will amplify the chance of identifying successful treatment strategies and allow comparison of treatment effects within an identical clinical context.

**Trial registration:**

EU Clinical trials register EudraCT Nb 2020-001614-38. Registered on 22 April 2020

**Supplementary Information:**

The online version contains supplementary material available at 10.1186/s13063-021-05033-x.

## Administrative information

The order of the items has been modified to group similar items (see http://www.equator-network.org/reporting-guidelines/spirit-2013-statement-defining-standard-protocol-items-for-clinical-trials/).

## Introduction

### Background and rationale {6a}

Since the beginning of the pandemic, the high disease burden and casualty rate of COVID-19 has prompted the quest for drugs that impact on the disease course. The aim of the Direct antivirals working against nCoV (DAWn) study protocols is to investigate promising drug compounds in a parallel series of proof-of-concept studies. All study protocols comply with the recommendations for outcomes as outlined by the WHO master template protocol (https://www.who.int/emergencies/diseases/novel-coronavirus-2019/technical-guidance/early-investigations and https://www.who.int/emergencies/diseases/novel-coronavirus-2019/global-research-on-novel-coronavirus-2019-ncov assessed on 17 June 2020).

The time pressure directs the search towards repurposing of existing molecules, besides the development of new drugs. Both a high viral load [1] and a disproportionate and prolonged cytokine response [2–4] seem to be correlated with worse prognosis. Herein lays the basis of the two most promising strategies for altering outcomes.

The first is the reduction of viral replication. In the Laboratory of Virology and Chemotherapy at the Rega Institute (KU Leuven), a library of existing drugs that were previously tested in clinical trials, of which some are available on the market, is being screened for compounds with in vitro activity against SARS-CoV-2. The drugs that are thereby identified are subsequently investigated in patients with COVID-19.

The second is the modulation of the immune response, with compounds that may directly alter the expression of implicated inflammatory cytokines (such as IL-1, IL-6, and TNF) [4, 5] or their upstream activation (such as the ACE2-dependent signaling) [6, 7]. The inseparable entanglement of inflammation and coagulation links both thrombotic macro- and mircroangiopathy to COVID-19 morbidity [3, 8, 9] and thus makes for an extra therapeutic target.

Currently, treatment strategies considered in the DAWN consortium are antiviral drugs, intensifying anticoagulation (e.g., with low molecular weight heparin), adding anti-inflammatory molecules (e.g., interleukin receptor antagonists, or C1-esterase inhibitors), or reconvalescent plasma.

One of the candidate drugs that may impact on COVID-19 is azithromycin. Azithromycin is a macrolide molecule with well-known anti-inflammatory and immunomodulatory effects in a broad range of respiratory and infectious diseases through modulation of innate and adaptive immune responses [10, 11]. Even more pertinent to this specific clinical context is the decreased mortality and time on ventilator shown in patients with sepsis-related acute respiratory distress syndrome [12].

In addition, azithromycin has a broad-spectrum in vitro antiviral activity, which has been documented for influenza, RSV, Zika, Ebola [13–18], and more recently SARS-CoV-2 [19]. However, the significance of this antiviral effect remains to be determined in vivo.

### Objectives {7}

The overall objective of the studies of the DAWn consortium is to evaluate the clinical efficacy and safety of investigational therapeutic agents in patients hospitalized with COVID-19. The multicenter DAWn-AZITHRO study will assess the efficacy and safety of azithromycin relative to the standard of care.

The primary outcome of all DAWn-studies will be clinical severity assessed as time to life discharge or to sustained clinical improvement measured according to the WHO master template for clinical studies to allow pooling of the data with other ongoing studies in and outside the consortium.

Secondary outcomes for DAWn-AZITHRO are clinical status and mortality during hospitalization and on days 15 and 29, time to events (ICU, death, discharge), duration of respiratory support, duration of hospitalization, duration of intensive care stay, occurrence of specific cardiac events (QTc prolongation, arrhythmia requiring intervention, reanimation, sudden cardiac death), and safety assessed by cumulative incidence of serious adverse events (SAEs) and adverse events (AEs) graded as grade 4 or 5, discontinuation or temporary suspension of drug administration (for any reason), changes in white cell count, hemoglobin, platelets, creatinine, glucose, total bilirubin, ALT, and AST over time.

Exploratory outcomes will be radiological and various functional evaluations 5–7 weeks post-discharge.

### Trial design {8}

DAWn-AZITHRO is a randomized, adaptive, open-label, multicenter clinical trial. The study is a phase 2 proof-of-concept trial. It compares standard of care (SOC) versus standard of care with azithromycin. Since there are no currently approved treatment options for COVID-19, the standard of care is mostly supportive. We refrained from defining the standard of care for the participating centers, and the adaptive protocol allows this to be changed according to new insights, which are regularly updated and summarized in national health recommendations (SCIENSANO). However, we demand that standard of care is predefined and not susceptible to treatment allocation. The clinical outcomes of this study have been chosen based on the outcomes of the WHO master template for clinical studies to allow pooling of the data with other ongoing studies.

The DAWn-AZITHRO will randomize with a 2:1 allocation to SOC + azithromycine versus SOC alone. 2:1 randomization is chosen to increase the appeal of the study after the considerable media attention for azithromycin. We presumed considerably less consent refusal, while only requiring a limited increase in sample size to retain power. Block randomization per group of 9 patients in every participating center will be implemented.

DAWn-AZITHRO will also add an exploratory study visit 5–7 weeks post-discharge for functional and radiological assessment (Fig. 1). All tests in the DAWN-AZITHRO protocol are part of standard clinical practice and good clinical follow-up.

**Fig. 1 Fig1:**
[figure not shown]
Trial design

## Methods: participants, interventions, and outcomes

### Study setting {9}

DAWn-AZITHRO is a multicenter study, recruiting patients in 15 Belgian hospitals, both academic and non-academic. All contributing hospitals have organized dedicated COVID wards and patients are recruited exclusively from these wards. The contributing institutions are:
University Hospitals LeuvenMariaziekenhuis Noord LimburgAlgemeen Ziekenhuis TurnhoutCentre Hôpitalier Universitaire-UCM NamurAlgemeen Ziekenhuis Nikolaas Sint-NiklaasOnze-Lieve-Vrouwzieknehuis AalstUniversity Hospital BrusselCliniques Universitaires Saint LucJan Yperman Ziekenhuis IeperHeilig Hart LeuvenAlgemeen Ziekenhuis KLINA BrasschaatAlgemeen Ziekenhuis Delta RoeselareAlgemeen Ziekenhuis Glorieux RonseHospitaux Iris Sud BruxellesSint-Lucas Brugge

### Eligibility criteria {10}

In short, participants eligible for inclusion are adult patients, hospitalized with COVID-19 disease. This means they have confirmed SARS-CoV-2 infection (either diagnosed with PCR or a typical pattern on chest CT) and disease signs (either clinical or radiological). Inclusion and exclusion criteria are summarized below; the fully detailed criteria are listed in the protocol (see Additional file 1).

Inclusion criteria:
Male or non-pregnant female adult ≥ 18 years of age at time of enrolmentHas a confirmed diagnosis of SARS-CoV-2 infection within 72 h prior to randomization, defined as either:
Laboratory-confirmed SARS-CoV-2 infection as determined by PCR, or other commercial or public health assay in any specimenorThe combination of upper or lower respiratory infection symptoms (fever, cough, dyspnea, desaturation) and typical findings on chest CT scan, and absence of other plausible diagnosesIllness of any duration, and at least one of the following:
Radiographic infiltrates by imaging (chest x-ray, CT scan, etc.), orClinical assessment (evidence of rales/crackles on exam) AND SpO2 ≤ 94% on room air, orRequiring mechanical ventilation and/or supplemental oxygenAdmitted to specialized COVID-19 ward or an ICU ward taking care of COVID-19 patients

Exclusion criteria:
ALT/AST > 5 times the upper limit of normalPregnancy or breast feedingAllergy to any study medicationAny medical condition which would impose an unacceptable safety hazard by participation to the studyHeart failure with severely reduced ejection fraction (≤ 30%)Known prolonged QT interval on ECG (> 470 ms males and > 480 females according to the Fridericia formula for corrected QT, or—in patients with ventricular conduction delay—the Rautaharju formula)Patients on macrolides during the last week before admission

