#### Criteria for discontinuing or modifying allocated interventions {11b}

QTc interval is monitored in patients at risk for long QT. When QTc exceeds 500 ms and/or QTc increases with more than 60 ms compared to baseline, azithromycin will be interrupted/discontinued at the discretion of the investigator. In case of intolerability of known side effects of azithromycin, interruption/discontinuation is left at the discretion of the investigator. Serious adverse events, or grade 4 adverse events according to CTCAE grading, are reported to the sponsor and further treatment decisions are discussed with the investigator case by case.

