#### Strategies to improve adherence to interventions {11c}

While hospitalized, drug administration is logged through the electronic medical prescription software. When patients are discharged from the hospital before the end of the treatment, they are asked to keep the empty blisters and return them by mail or on the next visit.

The protocol focuses on simple, but relevant clinical outcome parameters as primary and key secondary outcomes. Lab values, return visits, and exploratory outcomes are included, but need only be collected when clinically feasible. By this, we aim to ensure adherence to the minimal protocol requirements and proper data collection of these key measures, also in smaller centers without ample dedicated scientific personnel, in times where the burden of clinical tasks is especially high.

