### Secondary outcome

Status on an ordinal scale assessed daily while hospitalized and on days 15 and 29Cumulative clinical status up to day 15, i.e., sum of daily clinical status scores from days 1 to 15Time to events (ICU, death, discharge)Mortality on day 15 and day 29Duration of supplemental oxygenDuration of mechanical ventilationDuration of hospitalizationDuration of intensive care stayDate and cause of death (if applicable)NEWS assessed daily while hospitalized and on days 15 and 29Adverse events graded as grade 4 or 5 or SAEs, SARs, or SUSARsLab values: CRP, white cell count, absolute neutrophil count, absolute lymphocyte count, absolute eosinophil count, hemoglobin, platelets, serum creatinine, eGFR (CKD-EPI), hs-TroponinT, glucose, potassium, total bilirubin, ALT, and AST on days 1, 3, 5, 8, 11, 15, and 29 (if measured according to clinical indication)Combined cardiac endpoint (any of the following: hs-TroponinT levels > 0.5 ng/mL, ventricular arrhythmia requiring intervention, reanimation, sudden cardiac death)Follow-up of absolute QTc and delta QTc interval between baseline ECG and follow-up ECG at days 2–3 of treatment intervention, or with continuous ECG monitoring on ICU

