**Laboratory**								
CRP, hematology, chemistry, kidney and liver test	X	At clinician’s discretion	At clinician’s discretion				X^a^	
Pregnancy test for females of childbearing potential	X							
Viral qPCR (nasopharyngeal swab)				If feasible				

^a^If clinically feasible

^b^QT monitoring scheme: Long QT (> 470 ms males and > 480 females) is an exclusion for participation. In patients with no long QT on ECG but at risk, a QT monitoring will be performed with intermittent ECG monitoring at days 2–3 or continuous follow-up on ICUs. When QTc > 500 ms and/or delta QTc > 60 ms, IMP will be interrupted/discontinued at the discretion of the investigator. The patient’s medication will be reviewed daily to evaluate DDIs including drugs prolonging the QTc interval according to what is listed in the protocol (see Additional file 1)

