### Data collection and management

#### Plans for assessment and collection of outcomes {18a}

##### Collection of baseline parameters

After consent has been given, the following data are obtained retrospectively from the patient’s file: demographics, medical history, parameters and values of assessments from the moment of admission (vital signs, do not resuscitate (DNR)-code, clinical assessments, history taking, respiratory support, ECG, lab values). These should be obtained as part of routine clinical care. When study-related procedures impose an additional burden on the clinical care of patients, they can be waived. The assessment closest in time or most relevant to the situation at baseline will then be used instead.

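### The article intends a QTc check before azithromycin, but it excludes only a 'Known' prolonged QT and lets burdensome procedures be waived with no exception for the ECG

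*Protocol article*

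**What the plan says.** Two statements point to a QTc check before treatment.

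- In Participant timeline {13}, the ECG row is marked at Screen (day -3 to 0) and at Baseline (day 0). Unlike the lung function and CT rows, it does not carry the clinical-feasibility footnote.
- Footnote b to that table states: "Long QT (> 470 ms males and > 480 females) is an exclusion for participation".

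Section {11c} fits this reading. It lists what may be collected only when feasible, and the ECG is not on the list: "Lab values, return visits, and exploratory outcomes are included, but need only be collected when clinically feasible".

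Two other statements are looser.

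- The exclusion list in Eligibility criteria {10} reads "Known prolonged QT interval on ECG", with the same thresholds and the correction formulas.
- Collection of baseline parameters, under {18a}, lists what is taken from the patient's file, including "clinical assessments, history taking, respiratory support, ECG, lab values". It then says "When study-related procedures impose an additional burden on the clinical care of patients, they can be waived", and adds "The assessment closest in time or most relevant to the situation at baseline will then be used instead".

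The consent section {26b} gives the ECG as its first example of a study-related procedure.

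**The concern.** Adverse event reporting and harms {22} names long-QT syndrome as the main safety concern. It says the concern is met by the exclusion criteria and by ECG monitoring of patients at risk. The exclusion protects a patient only if someone reads a QTc before the first dose. If the criterion covers only a prolongation already known, and the ECG that would reveal an unknown one can be waived, the exclusion can be satisfied without any current QTc.

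The second safeguard does not fully cover this gap. Under footnote b, the ECG on days 2-3 or continuous monitoring is for patients judged at risk. A patient with an unrecognised long QT and no flagged risk factor could miss both. Relevant concomitant care {11d} leaves hydroxychloroquine to the investigator until the safety review after 80 patients, and the Discussion describes that drug as strongly QT-prolonging.

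A pre-dose QTc is also the reference for two later uses. One is the rule in {11b} on a rise of more than 60 ms "compared to baseline, azithromycin will be interrupted/discontinued at the discretion of the investigator". The other is the secondary outcome "Follow-up of absolute QTc and delta QTc interval between baseline ECG and follow-up ECG".

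**Working it through.** There is no figure in the plan to reproduce. The check sets the statements side by side.

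1. **Is a pre-dose ECG intended?** Yes. It is scheduled at Screen and Baseline, footnote b excludes any long QT, and {22} relies on the exclusion. Footnote b also sorts patients who have no long QT on ECG into at-risk and other, which presupposes that an ECG has been read.

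2. **Do the two statements of the exclusion agree?** The thresholds do: above 470 ms for men and above 480 ms for women. The condition does not. Section {10} requires the prolongation to be known; footnote b does not. Taken literally, a patient with no ECG on file passes {10}.

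3. **Does the waiver reach the ECG?** The ECG is in the baseline list of the same paragraph, and {26b} calls it a study-related procedure. The waiver is worded generally and the article gives no exception for the ECG. The Discussion's reference to mandatory QTc monitoring concerns the monitoring schedule and does not exempt the pre-dose ECG.

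4. **Does the substitute rule restore the check?** Not necessarily. It asks for the assessment nearest in time or most relevant to baseline. It sets no age limit and does not require a QTc to be read before dosing. The schedule places both randomization and the first dose on day 0.

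5. **Does any later step catch the omission?** None is stated. Investigators reassess eligibility ({26a}), but the article's criterion is the one worded 'Known'. Enrolment follows immediately on verbal consent ({16c}). Allocation is revealed once inclusion is confirmed and birth date and sex are entered ({16b}).

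For scale, the distance from the exclusion threshold to the absolute stopping limit is 500 - 470 = 30 ms for men and 500 - 480 = 20 ms for women. A patient wrongly admitted therefore starts less than that distance below the limit, or already above it. This shows why the entry check matters. It does not estimate risk.

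**The case against.** The strongest reply has three parts.

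**The eligibility list is a declared summary.** Section {10} refers to Additional file 1 for the full criteria, and that file may make a pre-dose QTc a condition of entry. This stands as a limit on the finding: if the file does so, only the article's wording needs aligning. It does not remove the conflict between {10} and footnote b. Nor does it touch the waiver, which is a separate rule and not part of the eligibility summary.

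**The intent is clear and the waiver belongs to data collection.** Read as a whole, the article describes a measured QTc at screening, and with an ECG done a prolonged QT becomes known. The waiver stands under baseline data collection, applies only where a procedure adds burden, and nowhere says that an exclusion may go unchecked. This is fair as to intent. The waiver's effect on the exclusion follows from its general wording and is not stated outright. But its words concern procedures being waived, not merely data left unrecorded, and no text sets safety tests apart.

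**Other protections remain.** These are the 500 ms limit, ECG monitoring in at-risk patients, daily medication review, and the exclusion for any condition that makes participation unsafe. This is correct and keeps the point minor.

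A reader might go further and infer that an ECG taken after the first dose could serve as baseline, hiding part of any drug effect in the azithromycin arm and biasing the delta-QTc comparison toward no difference. The documents do not support that. The text does not expressly bar a post-dose substitute, but the substitute must fit the situation at baseline, and the secondary outcome separates the baseline ECG from the follow-up ECG on days 2-3. Arguing that an ECG on day 1 or 2 is nearer to day 0 than one on day -3 does not help either, because it assumes that a pre-dose ECG exists.

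**Conclusion.** The point holds as a minor defect of wording with a safety consequence. The article's own statements, applied literally, allow a patient to be randomized and given azithromycin without a current QTc, although the schedule and footnote b intend otherwise.

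How often this would happen cannot be worked out from the article. It is probably rare, because the baseline assessments are expected from routine care. No effect on the primary outcome is claimed and no bias in the delta-QTc comparison is shown. No delay in stopping treatment is claimed either, since interruption is left to the investigator.

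The conclusion rests on two assumptions: that the waiver applies to the ECG because its wording is general and {26b} counts the ECG as a study-related procedure, and that nothing in the unseen full protocol overrides it.

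**What to change.** Delete 'Known' from the QT criterion in {10}, so that it agrees with footnote b.

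In Collection of baseline parameters, add a statement along these lines: *The screening ECG cannot be waived. A routine-care ECG from day -3 to 0 suffices, provided its QTc is read before randomization and the first dose. This pre-dose value is the baseline for delta QTc.* The last sentence also removes any doubt about a post-dose substitute.

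The thresholds and the discontinuation rule stay as they are. No procedure is added, because the ECG is already in the Screen and Baseline columns. The cost is that a few patients without a timely ECG may be delayed or not randomized; their number cannot be estimated from the article. If the full protocol already contains this requirement, the change is limited to aligning the article.
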